### Procedure

The study process flow is depicted in Fig. 1—“study process flow chart” and each step detailed in the following section of this protocol.

**Fig. 1 Fig1:**
[figure not shown]
Study process flowchart

#### Recruitment

There will be three layers of consent involved in this study: (1) when people undergo an interRAI assessment, they are asked to consent for their data to be used for planning and research; (2) when the assessing health care provider asks the person to give consent to be contacted by the research team; and (3) the person consents to take part in the trial.

Potential participants will be contacted via two pathways: (1) interRAI assessors will invite eligible older adults to participate in the study during their interRAI assessment home visit and (2) the local district health board will post letters to older adults who have recently had an interRAI assessment. The letters will outline a brief overview of the study with “Consent to Contact” (CtC) forms and free post return envelopes.

Once the research team has received the signed CtC forms, the study administrator will contact potential participants and explain the study in detail. The CtC form has two tick boxes whereby a potential participant can (1) permit the study team to contact their community pharmacist to confirm regular prescriptions of sedative or anticholinergic medications and (2) permit access to the electronic interRAI assessment record. This information will confirm the medication participants are taking at the start of the study.

The study administrator will confirm prescribed medications with participants during enrolment and their eligibility to participate in the study. If potential participants indicate verbally their willingness to take part in the study, a home visit by a study pharmacist will be scheduled. During visits, study pharmacists will explain the study to the potential participants, answer any questions, and obtain informed written consent to take part in the study.

Once consent to participate in the study has been received, each participant’s GP will be advised in writing that their patient has consented to take part in this study. Participants may withdraw from the study at any time.

#### Stratification

Using each consenting participant’s interRAI data, the Study Administrator will calculate their frailty index (FI) and classify each participant into one of the three frailty strata: low, medium, or high before the pharmacist’s visit. Details for the stratification methods can be found in the paragraph outlining the study design.

#### Randomization and allocation

Predefined randomization lists with a 1:1 allocation will be calculated by the study’s data manager using a Mersenne Twister algorithm. The algorithm will be repeatedly run until a list is identified that shows a difference in the total number of intervention and control arm participants of not more than three participants at any given point in the process. Centralized allocation is considered neither viable nor required in this community-based study setting, as the participants become available at random through the interRAI assessment process. The randomization list is securely stored on the university’s computer system and not available to any other research team member. Each frailty strata will have its randomization list and set of treatment allocations concealed in sequentially numbered sealed opaque envelopes. Allocations will be made by the study administrator, who will select the next allocation matching a participant’s frailty strata when the participant’s home visit is booked. The envelopes are opened after completion of the pre-intervention medication review. If a participant is discovered to be ineligible during the pre-intervention medication review, the corresponding envelope is returned and used with the next available participant.

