#### Access to data

The study data manager will have full unrestricted access to all study data throughout the trial. The study administrator and study pharmacists will have access to personal details to facilitate recruitment, consenting, and booking visits to participants. No other member of the research team will have access to personal details of study prospects or study participants. The senior pharmacist will have restricted access to data as required to perform data review duties throughout the trial. As a member of the Data Monitoring Group, the study statistician will have access to raw data held in REDCap to perform data quality checks. Blinding will be maintained throughout the trial.

After completing the trial and locking of data, the primary investigator and other named members of the research team will have access to de-identified study data. Data will not be shared with other researchers as per ethics approval and participant consent.

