### Blinding

Participants will be blinded to their study arm. The pharmacists conducting the first medication reviews will be blinded at the time of the medication review but made aware of allocation following the review when they open the envelopes at the first home visit. Pharmacists conducting post-intervention medication reviews will be blinded to the participants’ allocation in the follow-up home visits. Therefore, those pharmacists collecting medication data at either step will be blinded. Data collected for other outcome measures are collected independent of the study; thus, blinding is ensured. Patient unblinding is permitted in case of health concerns requiring immediate attention.

The study administrator and the data manager will have access to all participant data. The primary investigator and the study statistician will be blinded to participant data and allocation during the trial and unblinded following data verification and locking.

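### Random arrival does not conceal allocation; whether the administrator who screens, stratifies and picks the envelope can see past allocations is left contradictory, and the resulting risk is modest but cheap to remove

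*Protocol article*

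**What the plan says.** All references are to the protocol article.

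- **Reason for no central allocation** (Randomization and allocation): "Centralized allocation is considered neither viable nor required in this community-based study setting, as the participants become available at random".
- **List generation** (same section): "Predefined randomization lists with a 1:1 allocation will be calculated by the study’s data manager". The algorithm is re-run until a list shows "a difference in the total number of intervention and control arm participants of not more than three participants at any given point". Only the data manager has the list.
- **Concealment** (same section): "Each frailty strata will have its randomization list and set of treatment allocations concealed in sequentially numbered sealed opaque envelopes".
- **Administrator's tasks.** Recruitment: "The study administrator will confirm prescribed medications with participants during enrolment and their eligibility to participate in the study". Under Stratification, the administrator also computes the frailty index and assigns the stratum before the pharmacist's visit. Under Randomization and allocation, the administrator selects the next envelope for that stratum when the visit is booked.
- **What comes later.** The pharmacist takes written consent at the visit. The envelope is opened after the baseline medication review, and goes back for the next participant if the review shows ineligibility.
- **Administrator's access.** Blinding: "The study administrator and the data manager will have access to all participant data". The sentence after it names the primary investigator and the statistician as blinded to allocation during the trial; the administrator is not named. Access to data is narrower: "The study administrator and study pharmacists will have access to personal details to facilitate recruitment, consenting, and booking visits to participants".

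**The concern.** Concealment protects against one thing: that whoever decides who enters next, or when, knows or can guess the next arm. A random stream of arrivals gives no such protection, so the stated reason does not support the conclusion drawn from it.

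The point has practical weight because several pre-randomization steps meet in one role. The administrator confirms eligibility, assigns the stratum and ties a person to an envelope while consent and eligibility can still change. A sealed envelope stops its content being read. It does not stop inference from earlier allocations when the list has a balance limit. If the administrator sees those allocations, as the Blinding section can be read to allow, selection into arms becomes possible before the baseline review. It would bias the comparison of change in Drug Burden Index, and analysis could not reliably remove it.

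**Working it through.** **Inputs**

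- 1:1 allocation, with running difference "of not more than three participants at any given point in the process" (Randomization and allocation). I read the limit as applying to each stratum list, since each stratum has its own; the text does not settle this.
- List length 112 per stratum, 336 in all (Power and sample size).
- The article gives no predictability figure to reproduce.
- Assumptions: the guesser knows the limit and every earlier allocation in the stratum, and always guesses the arm that is behind.

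**Model**

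Re-running until the limit is met gives a fair random walk of 112 steps, conditioned on never leaving −3 to +3. Away from the end of the list, at current difference *s* the next allocation goes to the arm that is behind with probability

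cos(π(s − 1)/8) / [2 cos(π/8) cos(πs/8)].

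The table gives this probability and the share of allocations made at each absolute difference, from the exact 112-step calculation.

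| Difference before allocation | Share of allocations | Probability that the best guess is right |
|---|---|---|
| 0 | 25.5% | 0.50 |
| 1 | 42.8% | 0.59 |
| 2 | 24.5% | 0.71 |
| 3 | 7.2% | 1.00 |

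**Results with all earlier allocations known**

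- Certain in advance: 7.2%, or 0.072 × 112 ≈ 8 per stratum and 3 × 8 = 24 of 336.
- Correct guesses: 0.255 × 0.50 + 0.428 × 0.586 + 0.245 × 0.707 + 0.072 × 1.00 ≈ 0.62. The exact value, allowing for the end of the list, is 62.2%.
- Masked administrator: 50% correct, 0% certain.

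**Effect of envelopes still out**

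Envelopes are chosen at booking and opened at the visit, so a booked but unvisited participant in the stratum leaves the latest allocation unknown. The article does not say how many are usually outstanding, so I show a range.

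| Unopened envelopes outstanding in the stratum | Correct guesses | Certain |
|---|---|---|
| 0 | 62.2% | 7.2% |
| 1 | 60.1% | 0% |
| 2 | 57.9% | 0% |
| 4 | 54.6% | 0% |

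**Comparison with other schemes, nothing outstanding**

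| Scheme | Correct guesses | Certain |
|---|---|---|
| Stated rule (re-run whole list, limit 3) | 62.2% | 7.2% |
| Limit of 3 enforced step by step | 58.1% | 16.3% |
| Permuted blocks of 6 | 68.3% | 25.0% |
| Permuted blocks of 4 | 70.8% | 33.3% |

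The step-by-step version is shown only for scale; the article describes re-running the whole list.

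**The case against.** The case on the other side is substantial. The envelopes are numbered, sealed, opaque and separate by stratum. Only the data manager has the list. The pharmacist takes final consent, may find ineligibility, and is blinded during the baseline review. Strata follow preset cut-offs, which leaves little discretion. The rule is less predictable than ordinary small blocks, and pending bookings blur the count further. All of this stands and limits the size of the problem. None of it repairs the random-arrival argument or settles what the administrator can see.

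Three stronger readings are tempting, and the article does not support them:

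- **That the administrator is stated to see past allocations.** The Blinding section speaks of all participant data and does not mention allocation in that sentence; the next sentence names data and allocation as separate items. The Access to data section is narrower. The access is a fair inference from a contradiction, not a stated fact. Nor does the article say that the administrator knows the limit of three.
- **That the administrator controls the booking order.** Recruitment says only that a visit is scheduled. Entry depends on returned contact-consent forms, and pharmacists also have access for booking.
- **That the limit is tight and largely reveals the next arm.** The comparison with blocks of 4 and 6 shows otherwise.

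**Conclusion.** The point holds in limited form. The reason given for not needing central allocation is wrong as written. The two access statements conflict on a matter that decides whether allocation is concealed from the person who assigns envelopes.

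The size is modest. About 62% correct guesses and 7% certain allocations is an upper bound. It requires knowledge of the rule and of every earlier allocation, a limit that applies per stratum list, and no envelope outstanding. One outstanding envelope brings it to about 60% and none certain, and four to about 55%. If the administrator is masked, it is 50%. A reader might infer that selection bias has occurred or is likely; nothing in the article shows that. It shows only that the safeguard is argued on the wrong ground and is not secured in the text. The change is worth making because it costs so little.

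**What to change.** 1. Make the Blinding and Access to data sections agree: mask the arm field, and any record that reveals the arm, from the study administrator until database lock, and list this role as blinded to allocation.
2. Withhold the balance rule from recruiting staff, and state whether the limit of three applies per stratum list or to the trial total.
3. Delete the random-arrival justification. Sealed envelopes can stay, with the reasons for them that do hold: opaque numbered envelopes, a list held by the data manager alone, and opening after the baseline review.
4. The Trial status section expected recruitment to end on October 31, 2020. If it is complete, report whether the administrator could see allocations while enrolling.

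The cost is a REDCap permission change, plus moving any allocation-dependent task to the data manager or the pharmacist. Having the data manager release each envelope number during the home visit would go further, but it needs someone reachable at every visit and is not needed to resolve this point.

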#### Baseline medication review

Participants' medication use will be reviewed before the intervention and at least 6 months following the intervention. However, to avoid unnecessary complexity in obtaining prescribing records for people living in community settings, the focus will be given to the in-person review process in the participants’ homes. Here, the pharmacist will inquire about, view, and record the daily dose of all the participant’s medications.

#### Intervention arm

In the intervention arm of the trial, pharmacists will discuss with participants the medical conditions with which the DBI medications have been prescribed and their experiences with these medications. The consultation will determine if the potential harm of DBI medications prescribed outweigh their possible benefits. The participant and their family’s beliefs about the continued need for these medications and their preferences regarding willingness to discontinue these medications will also be determined via the consultation. After the consultation, target anticholinergic/sedative medications will be documented along with the participant’s concerns regarding these medications. Study pharmacists will consider the participants’ medical history as conveyed by the participants, their interRAI assessments, and their electronic medication records, if available.

The deprescribing implementation strategy that will be employed will focus on reducing or stopping anticholinergic and sedative medications to reduce participants’ DBI scores, using a process that was adapted from [2] and previously trialled in a New Zealand residential aged care setting [28, 29]. The process used in this study will differ from that used in the above residential care study because our study pharmacists will not have access to prescribing lists and clinical records before meeting the participants. Nevertheless, face to face consultations with the study pharmacists will capture rich data on participants’ medical history, medication lists, and their beliefs about their medications.

The deprescribing medication review will involve the following:
Pharmacist review of medication useParticipant consultationPharmacists suggesting changes in DBI medications to GPsGP consultation with the participantsGP decision to revise or not to revise DBI medication prescriptions

All medication reviews and DBI calculations will be reviewed and verified independently by a senior pharmacist (author [name]). All suggestions developed on potential deprescribing will be peer-reviewed by another study pharmacist before sending them to the participant’s GP, with additional expertise being available from the senior pharmacist.

Table 1 lists all the target medications considered for deprescribing in this trial, along with their corresponding anatomical therapeutic classification (ATC) code [30]. These medications are classified as anticholinergic or sedative based on The New Zealand Formulary [31]. This group of medications will encompass antipsychotics, anti-depressants, and benzodiazepines and non-benzodiazepine hypnotics.

#### Control arm

If allocated to the control arm, the pharmacist will conduct the medication review without discussing deprescribing options with participants. The control group participants will continue to receive routine care from their GP.

#### Clinical responsibility

Clinical responsibility for all participants remains with their primary care GP. Participants will be asked to contact their GP if they feel unwell during drug withdrawal. If disease relapse occurs or unwanted adverse drug effects occur, the medicine will be re-prescribed as seen appropriate by a participant’s GP.

Reasons for withdrawal or dropout, other than death, will not be recorded in the study. However, the research team will access and analyze hospital admissions. In addition, any notification of incidents received from participants or their GPs will be passed onto an internal data monitoring committee for review (data monitoring and safety are explained in the latter part of the document).

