### Outcomes

In this study, five outcome scenarios are possible: (1) completion of the trial, (2) entry into aged residential care (ARC) before completion (this would be linked to a change in GP and medication control), (3) prolonged hospitalisation, (4) death, and (5) withdrawal or other loss to follow-up. The first two outcome scenarios would involve the post medication review being undertaken either with the participant or via the medical records of a care facility. The third outcome scenario could lead to delays in recording the post-intervention review or may lead to any of the four other scenarios.

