#### Statistical analysis

The data analysis will use the intention-to-treat principle (where all available data, including records showing non-adherence to the protocol, from participants will be included in the analysis). Thus, imputation will not be used for missing data.

We will compare the proportions of the outcome measures using a chi-squared test and present results with a 95% confidence interval.

We will present Kaplan-Meier survival curves for analysis of hospitalizations, emergency department visits, entry into aged residential care, and mortality within subgroups. Subgroups will include control low frailty, control medium frailty, control high frailty, intervention low frailty, intervention medium frailty, and intervention high frailty. The analyses will be controlled for age and sex, with death as a censored event. We will then conduct a competing risk analysis using cumulative incidence functions (CIF). For example, where entry to aged residential care is the primary event of interest, death is the competing event. The CIFs are the probability of observing these events before the end of the 6-month follow-up period.

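### The protocol rules out recording why participants withdraw, so leaving because of symptoms after a medicine change cannot be told directly from unrelated leaving

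*Protocol article*

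**What the plan says.** Under Clinical responsibility, the protocol article sets an explicit rule: "Reasons for withdrawal or dropout, other than death, will not be recorded in the study". The same section foresees the events that could lead people to leave. It says "Participants will be asked to contact their GP if they feel unwell during drug withdrawal", and that after relapse or adverse effects "the medicine will be re-prescribed as seen appropriate by a participant’s GP". Recruitment adds: "Participants may withdraw from the study at any time".

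Statistical analysis defines intention-to-treat as an analysis in which "all available data, including records showing non-adherence to the protocol, from participants will be included in the analysis", and continues: "Thus, imputation will not be used for missing data".

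Outcomes lists five ways a participant's time in the trial can end: completion, entry into aged residential care, prolonged hospitalisation, death, and a residual group, "5) withdrawal or other loss to follow-up". On the follow-up measurement it says: "The first two outcome scenarios would involve the post medication review being undertaken". The first two are completion and residential-care entry. Primary outcome defines ΔDBI as the T1 value minus the T2 value, so a participant without a T2 review has no primary outcome.

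**The concern.** Only the intervention arm receives the deprescribing consultation and has recommendations sent to the GP (Intervention arm, Control arm). A participant who feels worse after a medicine change, has the medicine restarted and then leaves is a possible harm and probably also a non-responder on the primary outcome. Under the stated rule that person's record looks the same as that of someone who lost interest or moved away.

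Two things are at stake. The first is safety: leaving because of symptoms is information about the intervention, and reasons by arm would show it. The second is interpretation: when T2 DBI is missing and the analysis uses only what is available, the reader needs some basis for judging whether the missing values are related to outcome. Reasons for leaving are the most direct basis.

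This is a decision the article states, not a detail left to a fuller document. No later analysis plan can recover reasons that were never collected.

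**Working it through.** **Inputs.** From Power and sample size: 4% of controls and 14% of the intervention arm with ΔDBI ≥ 0.5, power 90%, α = 0.05, 167 per arm. The article states no dropout rate, so the loss rates below are assumptions.

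**The article's own figure.** For two proportions, two-sided α, unpooled variance:

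n = (1.960 + 1.282)² × [0.04 × 0.96 + 0.14 × 0.86] / 0.10² = 10.507 × 0.1588 / 0.01 = 166.9, so 167 per arm.

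This matches the stated number. The calculation contains no allowance for loss, so no expected dropout rate can be read from it.

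**Where the gap lies.** Setting Outcomes beside Clinical responsibility:

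| Way of ending | T2 review planned? | Reason known? |
|---|---|---|
| Completion | Yes | Not applicable |
| Entry into residential care | Yes, if necessary from facility records | Yes, by category |
| Prolonged hospitalisation | Possibly delayed, or becomes another category | Yes, by category |
| Death | No | Yes |
| Withdrawal or other loss | No | No, by rule |

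The gap is the last row. Clinical responsibility names death as the only exception to the rule, although Outcomes already separates two further categories. The wording of the two sections should be reconciled.

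**Illustration A: leavers counted as non-responders in both arms.** Suppose those with a T2 review show 14% v 4%, and 10% of each arm is lost.

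- Intervention: 0.90 × 0.14 = 12.6%
- Control: 0.90 × 0.04 = 3.6%
- Difference: 9.0 points instead of 10

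**Illustration B: loss in the intervention arm only, all non-responders.** If a share d leaves, a true rate p appears as p / (1 − d).

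| Assumed loss d | True 14% appears as | Apparent difference from 4% | Rejection rate if both arms truly 4% |
|---|---|---|---|
| 0% | 14.0% | 10.0 points | 5.0% |
| 10% | 0.14 / 0.90 = 15.6% | 11.6 points | about 5.5% |
| 20% | 0.14 / 0.80 = 17.5% | 13.5 points | about 7.3% |
| 25% | 0.14 / 0.75 = 18.7% | 14.7 points | about 8.9% |

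The last column uses the normal approximation to the pooled two-proportion test, with 167 controls at 4% and 167 × (1 − d) intervention participants at 0.04 / (1 − d). At d = 10% these are 150.3 participants at 4.44%. The pooled proportion is 13.36 / 317.3 = 0.0421, the null standard error 0.02258 and the actual standard error 0.02264. The two tails are 0.039 and 0.016, about 5.5% together.

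The two illustrations start from different places. A takes the observed rates as given and adds the leavers back; B takes the true rate as given and removes them.

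**The case against.** The strongest reply is that the article does hold other information on leavers. Clinical responsibility goes on to say that hospital admissions will be analysed and that notified incidents go to the data monitoring committee. Outcome data puts national dispensing records in the dataset, along with emergency presentations, admissions, residential-care entry and mortality. Data collection methods links secondary health data through the national health number rather than through study visits. Dispensing records bear directly on whether a medicine was restarted. Much of this stands, and it rules out the reading that the bias cannot be assessed at all. It does not close the gap. Admissions miss symptoms handled by the GP or endured at home, incident reports depend on someone volunteering them, and the article nowhere assigns dispensing records to classifying leavers or recovering their DBI.

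A reader might also infer that only completers are analysed. The article does not say that. Residential-care entrants are reviewed, non-adherent records are kept, and a participant whose medicine is restarted but who stays in the trial is measured at T2 and counted.

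Finally, a reader might attach worst- and best-case bounds to this point. With 10% missing per arm they run from 12.6 − 13.6 = −1 point to 22.6 − 3.6 = +19 points. The arithmetic is right, but these are the generic bounds for missing binary outcomes, and recording reasons would not change them. The lower end also needs every missing control to have a reduction of at least 0.5, against a planning rate of 4%. Under illustration A, with all 167 per arm, the difference still gives z = 0.09 / √(0.081 × 0.919 × 2/167) = 3.0.

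**Conclusion.** The point holds for the withdrawal and other-loss category. By a stated rule, the trial will not know why these participants left, and they have neither a T2 DBI nor an imputed one. It therefore loses a direct safety signal and the best available evidence on whether the missing outcomes are related to treatment. Linked data could probe the bias indirectly, so the correct statement is that direct assessment is ruled out and indirect assessment is not planned.

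The likely numerical effect is modest at moderate loss. At an assumed 10%, the difference moves from 10 to 9 points if leavers in both arms count as non-responders, or from 10 to 11.6 points if loss is confined to non-responders in the intervention arm. It grows with the loss rate and with imbalance between arms, neither of which the article gives. The figures show size under assumption and are not estimates of the bias in this trial.

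**What to change.** Replace the sentence under Clinical responsibility with a rule such as: the date of withdrawal or loss and, where the participant is willing, its main reason will be recorded in REDCap for both arms. The reasons should include feeling unwell or symptoms returning after a medicine change, being too ill to continue, no longer being willing, and not given. Moves into care are already captured and need only be cross-referenced.

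The study administrator should collect this, not the follow-up pharmacist. The Blinding section keeps that pharmacist unaware of allocation, and a reason that mentions a medicine change could reveal it.

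Report numbers and reasons by arm. Alongside them, prespecify a sensitivity analysis of ΔDBI ≥ 0.5 that counts missing DBI as no reduction, or takes it from the linked dispensing records where consent allows.

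The cost is one optional field and a short question when a withdrawal or loss is registered. Data collection methods schedules no study contact between T1 and T2, so the question must be tied to the notice of withdrawal. Some participants will give no reason. Trial status puts the end of recruitment at October 2020 and of data capture at May 2021. For people who have already left, only reasons already noted can be coded, and the report should state that limitation.
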